## Abstract

**Background:** Cardiovascular disease is the leading cause of mortality associated with diabetes, which is characterized by chronic hyperglycemia. Low-carbohydrate diet has gained popularity as an intervention in patients with type 2 diabetes mellitus, acting to improve glycemic profile and serum lipids. In its turn, exercise in hypoxia induces specific adaptations, mostly modulated via hypoxia-induced transcription factor signaling cascade, which increases with exposure to altitude, and promotes angiogenesis, glycogen supply, glucose tolerance, and raises GLUT-4 expression. **Aim:** Given that hyperglycemia decreases HIF-1α and it is better controlled when following a low-carbohydrate diet, this study aims to examine the hypothesis that a combination of both low-carbohydrate diet and chronic exercise in hypoxia in type 2 diabetes mellitus is associated with improved glycemic control and cardiovascular parameters, whose protocol is described. **Methods:** Patients with type 2 diabetes mellitus (*n* = 48) will be recruited and randomized into one of the three groups: (a) Control group: Control diet (low-fat and moderate-carbohydrate diet) + exercise in normoxia; (2) exercise in hypoxia group: Control diet + exercise in hypoxia; (3) intervention group: Low-carbohydrate diet (low-carbohydrate and high-fat diet) + exercise in hypoxia. Before and after 8 weeks of interventions, cardiopulmonary tests (Bruce protocol), body composition and blood pressure will be evaluated. Blood samples will be collected to measure hypoxia-induced transcription factor, C-reactive protein, glycemic and lipid profiles. **Summary:** This will be the first trial to examine the isolated and combined effect of chronic exercise in hypoxia and low-carbohydrate diet in type 2 diabetes mellitus. This trial will help to fill a significant research gap, guide future research and contribute to the combined nutrition and exercise approach to type 2 diabetes mellitus.

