Exercise in hypoxia (EH) has recently gained attention from the scientific community as a valuable therapeutic strategy (Millet et al., 2016). Actually, EH has been associated with health benefits in chronic obstructive pulmonary disease (Haider et al., 2009), coronary artery disease (Burtscher et al., 2004) and obesity (Urdampilleta et al., 2012). Chronic EH has been shown to influence some important mechanisms related to glycemic control, such as increasing hypoxia-induced transcription factor (HIF-1α), the activity of oxidative enzyme, glycogen supply, glucose tolerance and GLUT-4 expression (Faramoushi et al., 2016). These specific adaptations induced by hypoxia raise the question about the usefulness of EH as a therapeutic intervention in T2DM, but the evidence is still scarce.

HIF-1α appears to be a key element in the EH-induced adaptations, regulating the expression of genes associated with angiogenesis, such as vascular endothelial growth factor, vascular endothelial growth factor (VEGF) (Thangarajah et al., 2010). The low oxygen availability in EH promote the production of HIF-1α to a greater extent than when training under normoxia (sea-level) conditions (Desplanches et al., 1993). On the other hand, a high glucose environment impairs the activity of the HIF-1α. Thus, it is theoretically possible that a combined effect of LCD and EH works synergistically to improve T2DM, compared to the single effect of EH intervention, but the effectiveness of this hypothesis is currently unknown.

This article describes the protocol of a randomized, single-blind and parallel-controlled clinical trial that will evaluate the effects of chronic (8 weeks) EH, alone or combined with an LCD, on glycemic control and cardiovascular risk factors in patients with T2DM. The primary outcome of this randomized clinical trial (RCT) is to determine the effect of these interventions on hemoglobin A1c, while the secondary aims are to assess the impact on fasting blood glucose, plasma insulin and Homeostatic Model Assessment for Insulin Resistance (HOMA-IR), HIF1-α, cardiovascular risk factors and body composition. Due to a lack of well-conducted clinical trials, this study will provide original insights and important practical outcomes about EH and LCD interventions as non-pharmacological treatment modality in T2DM.

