This study aims to examine the hypothesis that a combination of both LCD and chronic EH in patients with T2DM is associated with improved glycemic control and cardiovascular risk factors, whose protocol is described.

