### Study design and setting

This is an 8-week, controlled, single-blind, three-arm, parallel, RCT, which will take place at the Faculty of Nutrition and Food Sciences and the Faculty of Sports of the University of Porto, at the Exercise Medical Center (CMEP) in Porto and at the Research Center in Sports Sciences, Health Sciences and Human Development (CIDESD) of the University of Maia. Participants will be randomly assigned into three independent groups (*n* = 16, in each) and the experimental design will consist of (a) pre-intervention tests, (b) familiarization period, (c) experimental intervention and (d) post-intervention tests.

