### Interventions

Volunteers who meet the inclusion criteria will be asked to sign a written informed consent before enrolment in the trial, with the principal researcher. Participants will be randomized into control (CTRL), EH or interventions (EH + LCD) groups during 8 weeks. The CTRL group will perform an exercise protocol in normoxia with a control diet, and the other groups will perform the same exercise protocol in hypoxia (simulated altitude – nitrogen dilution method), following a control diet (EH) or an LCD (intervention group). Thus, we will compare whether EH group is more efficient than exercise in normoxia (CTRL group) and, if by including a LCD (EH + LCD group) the effects of EH group would be potentiated. We emphasize that during all test, physical exercise professionals, nutritionist, and doctors or nurses will be available.

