### Statistical considerations

For sample and power calculations, this study is powered based on changes in hemoglobin A1c in RCTs included in the meta-analysis by Zuuren et al. (2018), which tested the effect of carbohydrate restriction up to 8 weeks. Considering a type I error of 5% and a power of 80% to detect differences at the dependent variable with a statistical significance when comparing 3 independent groups (CTRL versus EH and EH versus EH + LCD), and an effect size of 1.14, a sample size of 14 participants per group will be needed, totaling 42 individuals. With an assumption of a 20% dropout rate, we will recruit 48 participants. The sample size calculations were performed using the Statistical Power Analyses for Windows, (G*Power 3.1.9.4, Uni Kiel, Germany).

Statistical analysis will be performed using SPSS statistics software version 28.0, 2021 (IBM Company, Chicago, United States). All data will be reported as mean ± SD and statistical significance will be assumed at *p* ≤ 0.05. Pairwise comparisons will be analyzed using the Wilcoxon test. A two-way repeated measures ANOVA will be used to examine changes in cardiopulmonary parameters, body composition, glycemic profile, and cardiovascular risk factors over the chronic exercise period (0 vs. 8 weeks), and whether the magnitude of the chronic exercise-mediated adaptations differ between groups (EH vs. CTRL; LCD + EH vs. EH). When a significant main- or interaction-effect will be found, Bonferroni post hoc tests for multiple pairwise comparisons will be performed to identify differences between groups.

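### The abstract promises the isolated effect of the low-carbohydrate diet, but no arm gives the diet without hypoxia, so neither that effect nor synergy can be estimated

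*Protocol article*

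**What the plan says.** **Claim.** The Abstract (Summary) states: "This will be the first trial to examine the isolated and combined effect of chronic exercise in hypoxia and low-carbohydrate diet".

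**Arms.** Study design and setting: "This is an 8-week, controlled, single-blind, three-arm, parallel, RCT". Interventions: "The CTRL group will perform an exercise protocol in normoxia with a control diet". The other two groups train in hypoxia, "following a control diet (EH) or an LCD (intervention group". The diet therefore appears only together with hypoxia.

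**Joint action.** The Introduction says "it is theoretically possible that a combined effect of LCD and EH works synergistically to improve T2DM", with hypoxic exercise alone as the comparator. Interventions describes the third arm as showing "if by including a LCD (EH + LCD group) the effects of EH group would be potentiated".

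**Hypothesis.** The Abstract (Aim) and the end of the Introduction hypothesise that "a combination of both LCD and chronic EH in patients with T2DM is associated with improved glycemic control". Neither place says compared with what.

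**Contrasts.** Statistical considerations names the same two comparisons for the sample size and for the analysis, the latter as whether adaptations "differ between groups (EH vs. CTRL; LCD + EH vs. EH". It adds Bonferroni-adjusted pairwise tests after a significant main or interaction effect.

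**The concern.** Two factors are in play, hypoxia and diet, and three of the four possible combinations are run. The missing one, normoxia with the low-carbohydrate diet, is the one needed to see what the diet does by itself. It is also needed to judge whether diet and hypoxia together do more than the sum of the two.

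What is at stake is the reading of a positive EH+LCD vs EH result. The rationale is an interaction: high glucose impairs HIF-1α, hypoxia raises it, so lowering glucose might enhance the response to hypoxia. Yet the effect size used for the sample size comes from trials of carbohydrate restriction. A diet that works equally well with or without hypoxia would also produce a positive result, and the wording about potentiation invites reading it as an enhanced hypoxia effect.

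**Working it through.** **1. What the three arms identify.** Write the mean HbA1c change in each cell of the 2×2 layout as follows:

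- CTRL (normoxia, control diet) = m00
- EH (hypoxia, control diet) = m10
- EH+LCD (hypoxia, LCD) = m11
- normoxia with LCD = m01, not run

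Define H = m10 − m00 (hypoxia on the control diet), L = m01 − m00 (diet in normoxia) and I = (m11 − m10) − (m01 − m00) (interaction). Then:

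- EH − CTRL = H
- EH+LCD − EH = L + I
- EH+LCD − CTRL = H + L + I

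The third line is the sum of the first two, so there are two independent equations for three unknowns. H is identified. L and I appear only as the sum L + I.

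**2. Illustration (assumed values, not trial figures).** Take changes of 0 in CTRL, −0.3 in EH and −0.8 in EH+LCD, and vary only the unobserved cell:

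| m01 (not run) | EH − CTRL | EH+LCD − EH | EH+LCD − CTRL | I |
|---|---|---|---|---|
| −0.2 | −0.3 | −0.5 | −0.8 | −0.5 + 0.2 = −0.3 (synergy) |
| −0.5 | −0.3 | −0.5 | −0.8 | −0.5 + 0.5 = 0 (additive) |
| −0.8 | −0.3 | −0.5 | −0.8 | −0.5 + 0.8 = +0.3 (antagonism) |

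All three observable contrasts are the same in every row.

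**3. The plan's own sample size.** Inputs from Statistical considerations: effect size 1.14 (read as a standardised mean difference), type I error 5% (two-sided assumed, as the sidedness is not stated), power 80%. For a two-sample t-test the noncentrality is d√(n/2). At n = 14 this is 1.14 × √7 ≈ 3.02 on 26 degrees of freedom, giving power 82.7%; n = 13 gives 79.6%. The stated 14 per group therefore reproduces, as the size for one unadjusted pairwise comparison.

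**4. What a fourth arm would need.** The interaction contrast has variance 4·SD²/n with n per cell, so its noncentrality is d√n/2 on 4(n − 1) degrees of freedom. Interaction sizes of 1.14 and 0.57 SD are assumptions that show a range; alpha is 0.05 two-sided.

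| Interaction | Power at 14 per cell | n per cell for 80% | Evaluable total | With 20% dropout |
|---|---|---|---|---|
| 1.14 SD | about 55% | 25 | 4 × 25 = 100 | 100/0.8 = 125 |
| 0.57 SD | about 18% | 98 | 4 × 98 = 392 | 392/0.8 = 490 |

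The simple diet effect in normoxia would have about 83% power at 14 per cell if d = 1.14.

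**5. Cost of naming EH+LCD vs CTRL under an equal Bonferroni split (d = 1.14).** With two contrasts (alpha 0.025 each), power per contrast is 73% at 14 per group and 80% at 16. With three (alpha 0.05/3 each), it is 68% at 14 and 75% at 16, and 80% needs 18 per group.

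**The case against.** CTRL, EH, EH+LCD is a legitimate sequential add-on design, and its planned contrasts are sound. The abstract sentence is the only place that appears to promise an isolated diet effect. The Introduction and the Summary elsewhere describe hypoxic exercise given alone or with the diet, which fits the arms, and the Summary's closing discussion applies the word isolated to hypoxic exercise. The abstract also lists its arms, so a reader can see that none has the diet alone. This shows what may have been meant, but the sentence as written covers both components.

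Synergy is raised in the Introduction as a possibility whose truth is unknown, and no objective or analysis commits to testing departure from additivity. Potentiation can be read loosely as a larger effect once the diet is added, which EH+LCD vs EH does answer. Both points are fair. They rule out saying that the trial promises to demonstrate synergy, but they leave the interpretation of that contrast unguarded.

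A reader might also infer that the combination hypothesis has no planned test, because EH+LCD vs CTRL is not among the two named contrasts. The documents do not support this:

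- The hypothesis names no comparator. The Introduction, Interventions and item (c) of the novelties in the Summary set the combination against EH alone, and that contrast is planned.
- The Bonferroni pairwise tests could include EH+LCD vs CTRL, and novelty item (b), on normoxia against hypoxic exercise with or without the diet, leaves room for it.
- A fuller analysis plan, not shown, may list the contrasts.

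What remains is that this pair is not named in Statistical considerations and is not separately powered.

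**Conclusion.** The point holds as a mismatch between the abstract's claim and the design. The isolated effect of the diet, and any synergy or potentiation beyond additivity, cannot be estimated from these three arms at any sample size. This follows from the arm definitions and rests on no numerical assumption; the HbA1c values in the table are only illustrative. EH vs CTRL, EH+LCD vs EH and EH+LCD vs CTRL are all estimable, and nothing here invalidates them. The consequence is a limit on what may be concluded: EH+LCD vs EH measures the diet added during hypoxic training, and no more.

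**What to change.** 1. Reword the Summary in the Abstract to claim the effect of exercise in hypoxia and the added effect of the low-carbohydrate diet on top of it.
2. State in advance that a positive EH+LCD vs EH result will be read as the added effect of the diet during hypoxic training, not as synergy or potentiation. Adjust the Introduction and Interventions wording to match.
3. State the comparator for the combination hypothesis in the Abstract (Aim) and at the end of the Introduction.
4. Optional: if the whole-package effect is of interest, name EH+LCD vs CTRL in Statistical considerations. One suitable place is a secondary contrast after the two named ones, so that it takes no power from them and does not gate them. Placing it first in a fixed order is not free, because failure there would block both named contrasts. An equal three-way Bonferroni split lowers power per contrast to 68% at 14 per group.

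A fourth arm is not needed unless the isolated diet effect or synergy is to remain an aim, and a test of synergy would then need far more than 14 per cell. Items 1 to 3 change wording only, and item 4 uses data already planned. The downside is a less ambitious claim.

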## Introduction

The worldwide prevalence of type 2 diabetes mellitus (T2DM) in adults has increased from ∼150 million people in 2000 to >450 million in 2019, and is projected to rise further to ∼700 million by 2045 (Ogurtsova et al., 2022). Genetics and poor lifestyle behaviors, such as consumption of a high-sugar diet and a sedentary lifestyle, can have a predisposing influence on T2DM, which occurs at varying rates in people of different racial and/or ethnic backgrounds (Zhu et al., 2019). By definition, T2DM describes a group of metabolic disorders characterized by high blood glucose levels. People with T2DM are at an increased risk of developing a number of serious, life-threatening health problems, resulting in higher medical care costs, reduced quality of life, and increased mortality, mainly from cardiovascular diseases (Baena-Diez et al., 2016; Kelsey et al., 2022).

It is consensual that diet is the key strategy for preventing and managing T2DM. However, controversy still exists about the best dietary approach, namely the optimal macronutrient composition. A low-carbohydrate diet (LCD) has been proposed as a nutritional strategy with advantages in controlling glucose homeostasis and improving cardiovascular disease risk factors (Evert et al., 2019). Several studies have demonstrated improvements in markers of glycemic control and insulin sensitivity (Elhayany et al., 2010; Jenkins et al., 2018; Miyashita et al., 2004), and in serum lipids (Davis et al., 2009; Elhayany et al., 2010; Kirk et al., 2008) with broad-spectrum carbohydrates LCD (from 21 g daily up to 45% of daily energy intake). In addition to a healthy diet, exercise has been considered a cornerstone of T2DM therapy for many years (Colberg et al., 2016; Joslin, 1916). It is well established that regular physical activity is of paramount importance for the management of T2DM, as it has beneficial effects on the cardiometabolic risk factors involved in the development of diabetes complications (American Diabetes, 2000).

Exercise in hypoxia (EH) has recently gained attention from the scientific community as a valuable therapeutic strategy (Millet et al., 2016). Actually, EH has been associated with health benefits in chronic obstructive pulmonary disease (Haider et al., 2009), coronary artery disease (Burtscher et al., 2004) and obesity (Urdampilleta et al., 2012). Chronic EH has been shown to influence some important mechanisms related to glycemic control, such as increasing hypoxia-induced transcription factor (HIF-1α), the activity of oxidative enzyme, glycogen supply, glucose tolerance and GLUT-4 expression (Faramoushi et al., 2016). These specific adaptations induced by hypoxia raise the question about the usefulness of EH as a therapeutic intervention in T2DM, but the evidence is still scarce.

HIF-1α appears to be a key element in the EH-induced adaptations, regulating the expression of genes associated with angiogenesis, such as vascular endothelial growth factor, vascular endothelial growth factor (VEGF) (Thangarajah et al., 2010). The low oxygen availability in EH promote the production of HIF-1α to a greater extent than when training under normoxia (sea-level) conditions (Desplanches et al., 1993). On the other hand, a high glucose environment impairs the activity of the HIF-1α. Thus, it is theoretically possible that a combined effect of LCD and EH works synergistically to improve T2DM, compared to the single effect of EH intervention, but the effectiveness of this hypothesis is currently unknown.

This article describes the protocol of a randomized, single-blind and parallel-controlled clinical trial that will evaluate the effects of chronic (8 weeks) EH, alone or combined with an LCD, on glycemic control and cardiovascular risk factors in patients with T2DM. The primary outcome of this randomized clinical trial (RCT) is to determine the effect of these interventions on hemoglobin A1c, while the secondary aims are to assess the impact on fasting blood glucose, plasma insulin and Homeostatic Model Assessment for Insulin Resistance (HOMA-IR), HIF1-α, cardiovascular risk factors and body composition. Due to a lack of well-conducted clinical trials, this study will provide original insights and important practical outcomes about EH and LCD interventions as non-pharmacological treatment modality in T2DM.

This study aims to examine the hypothesis that a combination of both LCD and chronic EH in patients with T2DM is associated with improved glycemic control and cardiovascular risk factors, whose protocol is described.

## Material and methods

This article has been written in accordance with the SPIRIT (Standard Protocol Items: Recommendations for Interventional Trials) and CONSORT (Consolidated Standards of Reporting Trials) guidelines (Chan et al., 2013).

### Study design and setting

This is an 8-week, controlled, single-blind, three-arm, parallel, RCT, which will take place at the Faculty of Nutrition and Food Sciences and the Faculty of Sports of the University of Porto, at the Exercise Medical Center (CMEP) in Porto and at the Research Center in Sports Sciences, Health Sciences and Human Development (CIDESD) of the University of Maia. Participants will be randomly assigned into three independent groups (*n* = 16, in each) and the experimental design will consist of (a) pre-intervention tests, (b) familiarization period, (c) experimental intervention and (d) post-intervention tests.

### Eligibility criteria

To be included, participants must meet the following criteria: (a) Individuals of either sex diagnosed with type 2 diabetes by their medical doctor for at least one year; (b) hemoglobin A1c between 6.5% and 10%; (c) pharmacological regimen stabilized for at least three months; (d) previous participation in supervised exercise programs in the last 6 months, and (e) absence of smoking in the last 6 months. Participants will be excluded if: (a) They are insulin-dependent; (b) they have uncontrolled microvascular or macrovascular complications related to diabetes, such as retinopathy, nephropathy, diabetic foot and atherosclerosis, diabetic cardiomyopathy or acute myocardial infarction; (c) present other uncontrolled metabolic and vascular comorbidities; (d) are sedentary or (e) have physical limitation that prevent them from exercising. It is worth mentioning that medications, including doses and schedules, at baseline and changes throughout the study will be evaluated and documented.

### Recruitment

The recruitment period for this study will end in September 2023. After sample size calculation and clinical trial registration, participants will be invited to participate in the study through meetings, electronic and social media. The participant's timeline is shown in Figure 1.

**Figure 1. fig1-02601060231190663:**
[figure not shown]
Schematic diagram of participant visits during the study.

### Assignment of intervention

Participants confirmed as eligible will be randomized at a ratio of 1:1:1 to each group in blocks of four participants until complete the total number calculated (*n* = 48). A computer-generated random numerical sequence will be used for randomizing participants (Research Randomizer). The principal researcher will generate the sequence and conceal it in sealed, numbered opaque envelopes. Participants will be allocated a sequential number upon screening. The sealed envelope corresponding to the allocated participant number will be opened on the first visit by the principal researcher, and the participants will be allocated, without knowing which group they will belong to. As this is a single-blind study, blinding is not required for principal researcher, only to participants. A Consolidated Standards of Reporting Trials (CONSORT) flow chart outlining the study phases is displayed in Figure 2 (Moher et al., 2001).

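### A single fixed block size of four lets an unblinded researcher who takes consent and opens the envelopes predict later places in a block, even if someone else prepares the list

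*Protocol article*

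**What the plan says.** All of this comes from the protocol article.

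- **Study design and setting:** "Participants will be randomly assigned into three independent groups", with 16 in each and 48 in total. No strata are described.
- **Assignment of intervention, block rule:** participants are to be "randomized at a ratio of 1:1:1 to each group in blocks of four participants until complete the total number calculated". No variation in block size is stated, nor that the size is withheld from anyone.
- **Assignment of intervention, list and envelopes:** "The principal researcher will generate the sequence and conceal it in sealed, numbered opaque envelopes". Then: "Participants will be allocated a sequential number upon screening". Then: "The sealed envelope corresponding to the allocated participant number will be opened on the first visit by the principal researcher".
- **Assignment of intervention, blinding:** "blinding is not required for principal researcher, only to participants".
- **Interventions:** volunteers who meet the inclusion criteria "will be asked to sign a written informed consent before enrolment in the trial, with the principal researcher".

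**The concern.** A fixed block has a known stock of arms. Anyone who knows the block size and every earlier allocation can count which arms remain, and towards the end of a block the next one may be certain. Here that person is also the one with whom volunteers sign consent.

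If the next arm can be guessed, a borderline candidate can be taken in, delayed or discouraged according to the arm that is coming. That would bias the two planned contrasts, EH versus CTRL and EH + LCD versus EH, in the primary outcome HbA1c. It would also raise the false-positive rate.

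Two neighbouring faults do not cover this point. Moving list generation to an independent person leaves the counting possible. Correcting the block size because four does not divide by three could make matters worse, since the obvious correction, three, makes the last place of every block certain.

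**Working it through.** **Inputs.** From the article: three groups, 16 each, 48 in total; ratio 1:1:1; blocks of four; an unblinded researcher who sees each allocation. Assumed for steps 1 to 3: this person does not hold the list (generation has been moved), knows the block rule, and opens envelopes in order without gaps. A best guess means naming the most likely arm given the past; chance is 1/3.

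**Step 1. The plan's own figures.** 48/3 = 16 and 48/4 = 12 blocks, but 4/3 = 1.33. No block of four can be 1:1:1, and its make-up is not stated. Three readings are possible.

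**Step 2. Predictability under each reading.**

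*Reading A: each arm once plus a random fourth.*
- Place 1: 1/3.
- Place 2: a repeat has probability 2/4 × 1/3 = 1/6, so each other arm has (1 − 1/6)/2 = 0.417.
- Place 3: if the first two agree (1/6), the best guess is right half the time. If they differ (5/6), the missing arm comes next with probability (1/2)/(5/6) = 0.6. Together 1/6 × 0.5 + 5/6 × 0.6 = 0.583.
- Place 4: in half of the blocks the first three contain a repeat and the fourth is certain. Otherwise it is 1/3. Together 1/2 + 1/2 × 1/3 = 0.667.
- Mean: (0.333 + 0.417 + 0.583 + 0.667)/4 = 0.50. Certain places: 12 × 1/2 = 6.

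*Reading B: a 2:1:1 block in which the doubled arm rotates and is known.*
- Place 1: 1/2.
- Place 2: 1/2 × 1/3 + 1/2 × 2/3 = 1/2.
- Place 3: 1/6 + 5/6 × 1/2 = 0.583.
- Place 4: 1.
- Mean: (0.5 + 0.5 + 0.583 + 1)/4 = 0.646. Certain places: 12 × (1/6 + 1) = 14.

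*Reading C: four per arm, so blocks of 12.* Exact enumeration gives a mean of 0.512. Certain places: 4 × (0.006 + 0.055 + 0.273 + 1) = 5.3.

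**Step 3. Alternatives.**

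| Scheme | Certain places of 48 | Best guess right |
|---|---|---|
| Fixed blocks of three | 16 × 1 = 16 | (1/3 + 1/2 + 1)/3 = 61% |
| Fixed blocks of six | 8 × (0.2 + 1) = 9.6 | 56% |
| Random 3/6/9, set known | 0.035 × 48 = 1.7 | 55% |
| Random 6/9, set known | 0.050 × 48 = 2.4 | 54% |
| Random 6/9/12, set known | 0.024 × 48 = 1.2 | 52% |
| One permuted list of 48 | 0.030 × 48 = 1.4 | 43% |

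The random-size rows are simulated. The six and 48 rows are enumerated.

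**Step 4. Gaps from numbering at screening.** Suppose a fraction f of numbers is never opened (assumed; the article gives none). Under reading A, the fourth place is certain only if the three before it were opened, so 6 × (1 − f)³. With f = 0.2 this is 3.1, and with f = 0.4 it is 1.3. Simulated lists gave 2.9 and 1.2. Under reading B, the simulated figure falls from 14 to 7.8 and 4.0.

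**Step 5. Illustration of bias.** The outcome is N(0,1) with no true effect. The enroller shifts the expected outcome by d SD towards whichever of EH + LCD and EH is more likely next. The test is a two-sided 5% t-test of EH + LCD versus EH. The value of d is an assumption. With no shift, the simulated error rate is about 5%.

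| Scheme | Bias at d = 0.5 | Type I error at d = 0.5 |
|---|---|---|
| Blocks of four, A | 0.30 SD | 11% |
| Blocks of four, B | 0.54 SD | 28% |
| Blocks of three | 0.50 SD | 26–29% |
| Random 3/6/9, set known | 0.40 SD | 18% |
| One list of 48 | 0.19 SD | 7% |

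At d = 0.25 the type I error is about 6–12% for blocks of four and 5–6% for one list. With gaps (f = 0.2 and 0.4) and d = 0.5, reading A falls to about 8% at both rates, and reading B to about 24% and 15%.

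**The case against.** The strongest reply is that the simulated enroller is not the one in the article. The principal researcher generates the list, so all 48 allocations could be known whatever the block structure, and changing the blocks alone would protect nothing. This stands. It is why the fix must move list generation as well, and why this point ranks second to that one. For the same reason, publication of the block size adds nothing to what the list maker already knows. It matters only after the list has been moved.

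Four further objections stand in part.

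- Envelope numbers are given at screening, so unopened envelopes would blunt the counting, and the freedom to time consent is reduced. Step 4 shows that predictability shrinks but does not vanish. The article does not present this as a safeguard.
- The block make-up is unknown, and if four means four per arm the block is not small. Its last place is still certain.
- Randomly varied blocks are not a full answer. If the set of sizes is known, 3/6/9 does worse on best guess and bias than reading A (55% against 50%; 0.40 SD against 0.30 SD). What it removes is mainly the certain predictions.
- The article does not say who confirms eligibility. That the principal researcher controls entry is inferred from the consent wording, and some criteria, such as the HbA1c range, are objective.

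Fixed blocks are common, but this trial has no strata and a single list can give exactly 16 per group. The only thing small blocks add is balance over calendar time.

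**Conclusion.** The point holds as a secondary weakness of the allocation procedure. One fixed block size, combined with an unblinded researcher who takes consent and opens the envelopes, makes later places predictable well above chance. About 6 to 14 of 48 places are certain with blocks of four (about 5 with blocks of 12), against about 1.4 with one list. Best-guess success is 50–65% (51% with blocks of 12), against 43%. These figures assume ordered opening without gaps and are therefore upper-end.

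A reader might infer that the trial's type I error is as high as 28%, or that allocation will be steered. The documents support neither. The 28% needs both a known rotating fourth arm and a 0.5 SD shift used at every opportunity, and nothing in the article suggests intent. A reader might also infer that replacing the blocks is enough to conceal allocation. It is not, while the same person generates the list.

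**What to change.** In Assignment of intervention, replace the block phrase with wording such as: allocation follows one computer-generated random permutation of 48 places, 16 per group, generated and sealed by a team member who does not consent, enrol or open envelopes. The same randomisation tool and opaque envelopes will serve. Places on the list should be used only by people who are actually randomised. If screening failures use up numbers, a 48-place list no longer secures 16 per group.

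If balance over calendar time is wanted, use larger blocks in multiples of three, varied at random, with the sizes and their set withheld from the enroller. This mainly removes certain predictions; best-guess success stays near 52–55% if the set becomes known. Do not simply change four to three.

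If participants have already been randomised (the Recruitment section puts the end of recruitment at September 2023), keep their allocations and permute only the places still needed: 16 minus the number already in each group.

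The cost is one sentence, a new list and the task of preparing it for an existing team member. The downside is slightly less balance over calendar time.
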